## Methods

### Design

RECAP is a prospective cohort observational study. Data are remotely collected through a questionnaire form outlined in the original study protocol [5] for study-specific data, with additional demographic data being collected through routine electronic health record systems run by participating clinical practices.

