### Sample Size

#### Model Development and Internal Validation

Assuming that 10% of patients diagnosed with COVID-19 will be admitted to hospital [6], a 0.05 acceptable difference in apparent and adjusted Cox-Snell R-squared, 0.05 margin of error in estimation of the intercept, a binary outcome based on admission to hospital, and a maximum of 24 predictor parameters [5], we estimate that the minimum sample size required for new model development is 1317 participants enrolled for the development set [7].

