### Model Predictor Variables

The predictor variables to be included as candidates for the model have been decided through a Delphi process by the investigators and the research team, which are presented in Figure 1. The SNOMED codes are also outlined for these predictors. These predictor variables are contained in RECAP V0 [9], which include patients’ sociodemographic information (eg, age, ethnicity, adverse social circumstances) and comorbidities. The predictors that will be included in the primary model are continuous (heart rate, respiratory rate, trajectory of breathlessness, oxygen saturation at rest, oxygen saturation after 40 steps, temperature, time from first symptom [days], age, BMI) and categorical variables (profound tiredness or fatigue, muscle aches, myalgia, cognitive decline, being on a COVID-19 shielded list [10], gender, ethnicity, diabetes, hypertension, coronary heart disease, chronic kidney disease, and adverse social circumstance).

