#### Missing Data

The extent of missing data for each variable (outcome and predictors) will be assessed among all patients. Particular note will be taken of the potential for missing data in the oxygen saturation and temperature fields (in case the patient does not have instruments to measure these), and for respiratory rate (difficult to estimate unless independently counted visually) as these are considered particularly important factors for outcome.

If model outcome data are missing for >5% of the patients, methods to deal with missing data will be used and a sensitivity analysis to estimate the effect of using these methods will be carried out by comparing the estimated risk obtained without implementing a missing data method and the risk estimated using missing data methods.

The degree of missingness in predictor variables will be assessed. If the degree of missingness is above 50% for any predictor variable, then that predictor variable will be excluded from the model. If the degree of missingness is less than 50%, the data will be imputed using multiple imputation chain equations [18]. A total of 5 imputations will be performed and aggregated based on Rubin’s rules [19].

Data missingness mechanisms will be investigated to ascertain if the data are missing completely at random, at random, or not at random. This will be performed by considering the data structure to understand the dependency relationships between the missing data and the observed data. The missing data will then be described in relation to the degrees of missingness, missing data patterns, and possible reasons for missingness. We will also compare the characteristics of the patients with missing data and patients with complete data entries, which will allow us to assess the plausibility of the data missing completely at random. The distributions of the continuous predictor variables will be investigated for normality. Any missing continuous data that are not distributed normally will be transformed to a normal distribution for imputation and transformed back to the original scale for the final analysis.

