Multiple imputation chain equations [18,20] will be used, and all of the predictor variables (with less than 50% missing data) will be included in the imputation model. Variables without missing data will also be included, and the outcome variable (hospital admission) will be used for imputation of the predictor variables. We will use linear regression for continuous variables (normally distributed or transformed), and logit or ordinal logit regression for categorical variables. We will compare observed and imputed values, especially for variables for which the fraction of missing data is large [21].

The same imputation methods will be used in all datasets, for both continuous and categorical variables.

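### The imputation rule names no model for an unordered categorical predictor with more than two levels; if ethnicity has three or more groups, no listed method suits it

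*SAP article*

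**What the plan says.** The Missing Data section assigns linear regression to continuous variables and "logit or ordinal logit regression for categorical variables". It adds: "The same imputation methods will be used in all datasets, for both continuous and categorical variables". On scope it says that "all of the predictor variables (with less than 50% missing data) will be included in the imputation model", so ethnicity is imputed whenever some of its values, but fewer than half, are missing. Pooling is fixed too: "A total of 5 imputations will be performed and aggregated based on Rubin’s rules".

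Model Predictor Variables names ethnicity among the categorical predictors of the primary model: "being on a COVID-19 shielded list [10], gender, ethnicity, diabetes, hypertension, coronary heart disease, chronic kidney disease, and adverse social circumstance". The text available does not give the number of ethnic groups (Figure 1 could not be seen), does not say which imputation model applies to which variable, and gives no missing fraction for ethnicity.

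**The concern.** The list of imputation models has a gap. Binary logit accepts two levels. Ordinal logit accepts more, but assumes they form a ranked scale along which each covariate moves every patient in one direction. Ethnic groups have no such ranking. With three or more groups, the only listed model that accepts the variable imposes an order that comes from the code list and not from the data.

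Ethnicity is a candidate predictor kept or dropped at P<.05 under Objective 1, so distorted ethnicity terms could affect selection as well as the coefficients. The same rule applies to the external validation data, so validation might not expose the distortion. The planned subgroup checks concentrate on age and gender.

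**Working it through.** **No stated figure depends on this.** No sample size or precision target in the plan uses the imputation model, so there is nothing to reproduce. Two checks apply: whether the document reveals how ethnicity is coded, and how much code order can matter.

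**1. Does the parameter count reveal the coding?** The sample size section allows "a maximum of 24 predictor parameters". Model Predictor Variables lists 9 continuous and 12 categorical predictors: 9 + 12 = 21, counting one parameter each. Objective 1 adds 3 interactions: 21 + 3 = 24. That fits a two-group ethnicity. But if the 24 − 21 = 3 spare parameters went to ethnicity and not to the interactions, ethnicity would have 1 + 3 = 4 indicator terms, enough for five groups. The count also ignores extra fractional polynomial terms. It does not settle the coding.

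**2. The two models.** For K groups and covariates x:
- Ordinal logit: logit P(E ≤ k) = α_k − x′β, with one β shared by all thresholds.
- Multinomial logit: log[P(E = k)/P(E = reference)] = α_k + x′β_k, with a separate β_k per group.

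Relabelling the groups leaves the multinomial fit unchanged. In the ordinal model it changes which groups are neighbours, and so changes the fitted probabilities.

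**3. Simulation. All inputs are assumptions.** n = 40,000; a reference group R and groups 1 to 4 with shares 45, 25, 12, 6 and 12%; true log odds ratios of 0.5, 0.7, 0.1 and 0.3 for groups 1 to 4 against R; age and a binary social covariate that differ by group; 8.9% admitted; missingness of ethnicity depends on age. Ethnicity was imputed 5 times from age, the social covariate and admission. This is one replicate without parameter draws, so only point estimates are compared. Code orders: A = R,1,2,3,4; B = 1,3,R,4,2; C = 1,2,4,3,R.

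| Log odds ratio vs R | Group 1 | Group 2 | Group 3 | Group 4 |
|---|---|---|---|---|
| Full data | 0.38 | 0.59 | −0.03 | 0.26 |
| 40% missing, multinomial | 0.40 | 0.65 | −0.01 | 0.32 |
| 40%, ordinal A | 0.31 | 0.50 | 0.10 | 0.32 |
| 40%, ordinal B | 0.21 | 0.38 | −0.07 | 0.14 |
| 40%, ordinal C | 0.41 | 0.52 | 0.04 | 0.24 |
| 20% missing, multinomial | 0.46 | 0.64 | 0.07 | 0.31 |
| 20%, ordinal A | 0.40 | 0.56 | 0.11 | 0.34 |
| 20%, ordinal B | 0.36 | 0.48 | 0.02 | 0.24 |
| 20%, ordinal C | 0.44 | 0.57 | 0.06 | 0.29 |

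Spread across code orders (largest minus smallest):
- 40% missing: 0.41 − 0.21 = 0.20; 0.52 − 0.38 = 0.14; 0.10 − (−0.07) = 0.17; 0.32 − 0.14 = 0.18.
- 20% missing: 0.08, 0.09, 0.09 and 0.10.

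At 20% the multinomial estimates themselves differ from full data by up to 0.07 − (−0.03) = 0.10 in this single replicate. The comparison between methods on the same missing records is therefore more informative than the comparison with full data.

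**4. Larger sample.** A second simulation (n = 120,000, 3 replicates, missing completely at random, five groups, true log odds ratio 0.5 for two groups and 0 for two others) used a single code order. For one group with a true effect and one without:
- 40% missing: 0.42 (full data 0.51) and 0.19 (full data −0.03).
- 20% missing: 0.44 (full data 0.50) and 0.09 (full data −0.03).
- 10% missing: 0.48 and 0.02, against assumed true values of 0.5 and 0.

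Multinomial logit stayed close to full data throughout. In two further simulations, also with assumed inputs, the largest shifts at 10% missing were about 0.08 and 0.10.

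**The case against.** **A reader might infer that ethnicity will be imputed by ordinal logit.** The document does not say so. Its list is generic and ties no model to any variable, and logit can be read loosely to include multinomial logit. That reading is possible but not natural, because the ordinal form is named separately and the multinomial form is not. The gap in the list stands; the claim that ordinal logit will be used does not.

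**The deciding facts are not visible.** Two-group coding is compatible with the parameter count. Missingness in ethnicity may also be slight: the plan flags oxygen saturation, temperature and respiratory rate, and the Design section describes "additional demographic data being collected through routine electronic health record systems run by participating clinical practices". Both points stand and make the concern conditional.

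**A reader might also infer that RECAP-V1 will be miscalibrated by ethnic group.** This was not shown. The simulations used a handful of covariates, and no full model with vital signs was fitted. No effect on discrimination, calibration curves, Brier score or the red/amber/green cut-offs was demonstrated. Sampling error at the actual size is also large. In iCare (2429 patients), an assumed 8% group has about 0.08 × 2429 = 194 patients and, at an assumed 6.6% admission, about 13 admissions. The standard error of its log odds ratio is then roughly 0.3. The shift of 0.09 − (−0.03) = 0.12 at 20% missing is about 0.4 standard errors, and 0.19 − (−0.03) = 0.22 at 40% is about 0.7.

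**The plan has partial safeguards.** It will compare observed with imputed values and will explore machine-learning imputation alongside the traditional method. The first is weak here. In one simulation at 40% missing, imputed group shares matched observed shares within 0.5 percentage points under every code order while the coefficients moved; the error lies in the association with admission, not in the distribution. The second is exploratory and does not correct the primary specification.

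**Conclusion.** The point holds as a gap in a stated rule. The listed models cover binary and ordered predictors only, and a predictor the plan names may be neither. If ethnicity has three or more groups and the text is followed literally, its coefficients depend on code order. Under the assumed inputs this is small at about 10% missing, about 0.1 on the log odds scale between code orders at 20%, and up to 0.20 at 40%. With two groups it vanishes. Severity is minor, conditional on three or more groups and appreciable missingness. No stated sample size is affected.

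**What to change.** Reword the sentence in Missing Data to: logit for binary variables, ordinal logit for ordered variables, and multinomial (polytomous) logit for unordered variables with more than two levels, such as ethnicity. State the ethnicity categories next to the predictor list, or state that ethnicity is coded in two groups. Apply this in all four datasets. The mice package already named under Software offers it as method polyreg.

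The cost is one sentence and one method setting, plus more coefficients in the ethnicity imputation model. With K groups and p covariates, ordinal logit has (K − 1) + p coefficients and multinomial logit (K − 1)(p + 1). For an assumed K = 5 and p = 21 (the 20 other predictors plus admission, one term each), that is 4 + 21 = 25 against 4 × 22 = 88. Very small groups may therefore need merging before imputation, by a rule set in advance.

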#### Exploratory Analyses

We are planning to conduct exploratory analyses given the unique data collected in the study.

A time to event data model will be constructed using Cox regression of time to hospital admission. The model will be analyzed as time-series survival data by fitting a subdistribution hazard model [22] to account for deaths from any other causes that generate censored data in the results. This will be achieved by taking the time to admission for each patient. The discrimination of the models will be assessed using the Harrell C and Somer D statistics to measure the association of the ordinal logistic regressions.

A set of alternative risk estimates will also be explored in the possible scenarios for which temperature measurement, oxygen saturation at rest or on exercise, or respiratory rate are missing. It is expected that temperature, oxygen saturation, and respiratory rate might be at high risk of missingness, as in practice these factors might be hard to record. Hence, we will develop a prediction model in the case that these data are missing completely. This will also allow us to investigate the importance of these data for prediction of the risk of hospital admission.

A prediction model will be built using machine learning (ML). We will use nonlinear classifiers, including random forest and gradient tree boost algorithms, as well as a recurrent neural network to build a predictive model based on time-series data, as we expect there may be a nonlinear relationship between the predictors and the discrete outcomes. We will use 10-fold cross-validation with hyperparameter tuning by a grid search. RECAP-V1 built using logistic regression and the prediction models built using ML will be compared based on diagnostic accuracy estimates. ML methods for missing data imputation will also be applied. For this purpose, we will use random forest–based algorithms, DataWig, and generative models (generative adversarial networks), which have been shown to be superior to traditional missing data imputation techniques [23-25]. These ML methods will be compared to traditional missing data imputation.

Mortality and admission to the intensive care unit (ICU) will also be modeled. Two definitions of death from COVID-19 will be used: (1) death as a result of severe COVID-19 or COVID-19 complications in a hospital setting, and within 28 days of illness onset; and (2) death in a different setting (either after hospital discharge or in patients that were not admitted) within 28 days of illness onset, where COVID-19 is mentioned as a contributor in the death certificate of the patient. We will investigate the number of events for death and admission to the ICU, and determine if we have sufficient power to build predictive models for death and admission to the ICU.

Finally, we will explore combining the CCAS dataset to the primary iCare dataset to increase the power of the model. Differences in the patients between the datasets will be quantified, as well as exploring the effect that adding this additional dataset to the model would have on the performance of the model through internal-external cross-validation stratified for which dataset the patients’ data originated to ensure the transferability of the predictions for different subpopulations [16,26,27].

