## Introduction

### Trial Background and Rationale

Since the start of the pandemic, there has been extensive work [1-3] to develop risk scores for the management of patients with acute COVID-19 that can help to predict the risk of hospitalization, deterioration, and death.

There is pressure on clinical services, and evidence that a small percentage of patients experience precipitous deterioration (usually on about day 7 after symptom onset) [4]. For this reason, there is a growing clinical need to develop and validate an early warning risk tool to be used in a primary care setting that is specific to COVID-19 and based on data that can be reliably collected during a remote consultation.

The RECAP (Remote COVID-19 Assessment in Primary Care) trial (NCT04435041) was designed to develop an early warning tool for patients diagnosed with COVID-19 in primary care settings. The original study protocol [5] outlines the study rationale and data collection process. This paper describes the process for quantitative development and validation of the RECAP-V1 model. The primary objective is to produce a multivariable risk prediction tool to facilitate primary care physicians and other clinicians working in the community in the early identification of COVID-19 patients that are at higher risk of requiring hospital admission, and to inform the early escalation of their treatment, with the aim to expedite admission where necessary and decrease deaths.

To minimize the risk of data selection bias and data-driven interpretation of results, we here outline a prespecified statistical analysis plan (Version 1.0), which details all of the analysis steps to develop and validate the risk prediction model.

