### Population Data

The data are collected in four different systems: (1) iCare (North West London Whole Systems Integrated Care), which is the Imperial analytics platform for high-paced processing of patient data from North West London practices; (2) the Royal College of General Practitioners (RCGP) Research and Surveillance network (RSC Practice network), which is a general practice sentinel network that collects data from practices across England and Wales; (3) NHS111 CCAS; and (4) DoctalyHealth Care, a home monitoring service for patients with a diagnosis of COVID-19.

The data will be collected using templates embedded in health record systems used in routine contacts for patients with suspected COVID-19, and then the records will be linked between primary and secondary care. The consent for this data linkage will also be collected. Once recruited, patients will be followed up for 28 days after the COVID-19 diagnosis.

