### Model Outcome Variable

The outcome variable considered in building the risk model RECAP-V1 is hospitalization within 28 days following a positive ascertained diagnosis of COVID-19 (either a clinical diagnosis or a polymerase chain reaction test).

Hospitalization is defined as a patient being admitted and having spent at least one night in a bed in a hospital in the period following a COVID-19 diagnosis and up to 28 days following the diagnosis.

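### The exploratory death outcome is counted for 28 days from illness onset, but follow-up and admission run 28 days from diagnosis, so later presenters get a shorter death window

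*SAP article*

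**What the plan says.** Under Exploratory Analyses, the SAP plans to model mortality and ICU admission if there are enough events. It gives two definitions of COVID-19 death. The first is "death as a result of severe COVID-19 or COVID-19 complications in a hospital setting, and within 28 days of illness onset". The second covers deaths elsewhere ("either after hospital discharge or in patients that were not admitted) within 28 days of illness onset") where the death certificate names COVID-19 as a contributor. Both clocks start at illness onset.

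The rest of the SAP uses a different clock:

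- Population Data: "Once recruited, patients will be followed up for 28 days after the COVID-19 diagnosis".
- Model Outcome Variable: the outcome is "hospitalization within 28 days following a positive ascertained diagnosis of COVID-19", and the definition of an admission repeats that origin: "in the period following a COVID-19 diagnosis and up to 28 days following the diagnosis".

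Onset and diagnosis are not treated as one moment. Trial Background and Rationale places deterioration "usually on about day 7 after symptom onset". Model Predictor Variables includes "time from first symptom [days], age, BMI" among the continuous predictors, and time from first symptom is informative only if it varies between patients. The SAP does not explain why death has its own origin. It also does not say how to classify a death that falls after day 28 from onset but before day 28 from diagnosis.

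**The concern.** A risk estimate made at a consultation needs one horizon that starts at about that time. With the onset clock, the horizon for death shrinks by one day for each day the patient has already been ill, so its length is fixed by a quantity the SAP lists as a candidate predictor. Three things are at stake:

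- **Event count.** Deaths observed within follow-up are recoded as non-deaths, and the number of deaths decides whether a mortality model is built at all.
- **Comparability.** Death and admission predictions for the same patient would cover different periods, and the difference would vary from patient to patient.
- **Bias.** The loss grows with delay, so death risk is understated most in late presenters. If time from first symptom is a predictor, part of its coefficient reflects the outcome definition and not the disease.

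**Working it through.** There is no SAP figure to reproduce: no sample size or event number is given for mortality. The check has one part that needs no assumptions and two that do.

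**1. Window length (no assumptions).** Let t be the days from onset to diagnosis. A death counts up to day 28 from onset, which is day 28 − t from diagnosis. Follow-up and admission run to day 28 from diagnosis.

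| t (days) | Death window after diagnosis | Shortfall, t/28 |
|---|---|---|
| 0 | 28 | 0% |
| 3 | 25 | 11% |
| 7 | 21 | 25% |
| 10 | 18 | 36% |
| 14 | 14 | 50% |
| 21 | 7 | 75% |

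Example: a patient diagnosed on illness day 10 who dies 20 days later dies on illness day 30. That is inside follow-up, but the death is counted under neither definition.

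**2. Share of deaths dropped (timing of death assumed).** The SAP gives no distribution of time to death. Let T be onset-to-death time with distribution function F. Among deaths within 28 days of diagnosis, the share lost is

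[F(28 + t) − F(28)] / [F(28 + t) − F(t)].

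Take T lognormal with median 18 days and sigma 0.5. At t = 7, F(7) = 0.0295, F(28) = 0.8116 and F(35) = 0.9082. The share is (0.9082 − 0.8116) / (0.9082 − 0.0295) = 0.0966 / 0.8787 = 11.0%. The same formula gives 4.1% at t = 2, 14.9% at t = 10 and 22.1% at t = 14.

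Both parameters were then varied, with medians of 15 to 21 days:

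| Assumption | Dropped, t = 7 | Dropped, t = 10 |
|---|---|---|
| sigma 0.5 | 6.8–15.5% | 9.8–20.3% |
| sigma 0.3 to 0.6 | about 2–16% | about 2–21% |

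The shape of the distribution also matters. With gamma onset-to-death times (means 14 to 20 days), 4–13% is dropped at t = 7 and 9–24% at t = 14. If instead the hazard after diagnosis does not depend on delay, the loss is 2–25% at t = 7 and 11–50% at t = 14; the upper ends are for a constant hazard. In every case the loss grows with t.

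**3. Effect on the coefficient of delay (further assumptions).** One million patients were simulated with delays averaging 6 days (5th to 95th percentile 1 to 13), a 2% risk of death within 28 days of diagnosis, and no true effect of delay on the hazard after diagnosis. A logistic model of death on t gave these odds ratios per 7 days:

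| Time to death after diagnosis | Onset clock (as written) | Diagnosis clock |
|---|---|---|
| Constant hazard | 0.70 | 0.99 |
| Gamma, mean 11 days | 0.85 | 1.02 |

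If the hazard instead runs from onset, part of the fall in risk with delay is genuine. For the lognormal with median 18 and sigma 0.5, the probability that a fatal case dies in the window after diagnosis is:

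| Window | t = 0 | t = 7 | t = 14 |
|---|---|---|---|
| Onset clock | 0.81 | 0.78 | 0.50 |
| Diagnosis clock | 0.81 | 0.88 | 0.65 |

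From t = 7 to t = 14 the fall is about 36% with the onset clock (1 − 0.50/0.78) and about 26% with the diagnosis clock (1 − 0.65/0.88). The onset clock steepens the decline but does not create all of it.

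**The case against.** The strongest reply accepts that the clocks differ and disputes how much follows from it.

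- **Reach.** Mortality modelling is exploratory and conditional on event numbers. The research questions, primary outcome, sample size, cut-off points and external validation all concern hospitalization. This stands and limits the point.
- **Coefficient.** A reader might infer that the SAP's mortality model will report a spurious protective effect of longer symptom duration. The SAP does not support that as fact. It lists time from first symptom for the primary model and names no predictors for mortality. Part of any decline with delay would be survival to presentation, which a diagnosis clock keeps. The net sign depends on delays and on any real effect of delay, neither of which the SAP gives. What stands is a direction of bias, if the predictor is carried over.
- **Late deaths.** A reader might also argue from deterioration around day 7 that deaths fall late and are mostly the ones cut off. The background section says nothing about time to death, so this cannot be drawn from it.
- **Size.** Varying only the median makes the loss look better known than it is. Letting sigma vary as well lowers the bottom of the range to about 2%. Because no delay distribution is given, the overall share of deaths lost is unknown and could be small.
- **Legitimacy.** Death within a fixed time of onset is a coherent measure of mortality over the disease course. That is true, but the SAP does not state this aim, and such a measure needs an analysis that handles unequal observation after diagnosis.

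None of these replies removes the unequal windows or the recoding of deaths seen within follow-up.

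**Conclusion.** The point holds for the exploratory mortality analysis. From the SAP's text alone, the death window after diagnosis is 28 − t days against 28 for follow-up and admission, and deaths in the gap become non-deaths. The feasibility count is lowered by whatever number of deaths falls there, and patients do not share one prediction horizon.

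The size rests on assumptions. With a lognormal onset-to-death time (median 15–21 days, sigma 0.3–0.6), about 2–16% of deaths within 28 days of diagnosis are lost for diagnosis on day 7, and about 2–21% on day 10. If time from first symptom is used in the mortality model, and is taken to measure the onset-to-diagnosis delay, its coefficient is biased in the protective direction. Neither the amount nor the resulting net sign can be fixed from the SAP.

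The primary hospitalization model is anchored at diagnosis and is not affected. The correction should be made, but it does not threaten the main result.

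**What to change.** In Exploratory Analyses, change the end of the window in both death definitions from 28 days of illness onset to 28 days of COVID-19 diagnosis. State the same window for ICU admission, for which that section gives none. Time from first symptom can then serve as a predictor without also setting the length of the outcome window.

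If mortality over the disease course from onset is what is wanted, say so, give the reason, and analyse it as time to event with delayed entry at diagnosis. Unequal observation is then handled in the model.

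The first option costs two changed phrases and one added window. It needs no new data, because planned follow-up already reaches 28 days from diagnosis. The second needs a short description of the model.
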